### Therapist training and fidelity

The therapists in the current trial are crisis team health care workers. They attend a 1-day seminar held by the originator of CIPE ([name]) or the study PI. The seminar consists of a thorough lecture on the theoretical basis of, and every intervention included in CIPE, as well as practical skills training in CIPE interventions. All therapists receive the CIPE treatment manual (unpublished). As all CIPE treatment components are delivered through standardized text, therapist drift is not possible other than in the secure emails. Continuous monitoring of therapist fidelity in these emails is thus accomplished by two senior consultant clinical psychologists, as well as the trial PhD/clinical psychologist (all trained in CIPE).

### Contamination

For organizational and practical reasons, the majority of the crisis team therapists deliver both TAU and CIPE. Consequently, there is a risk of contamination across conditions at the therapist level. To reduce the risk of contamination, therapists are repeatedly instructed and reminded not to mix the conditions, and are prohibited from using the CIPE internet platform outside of the timeframe of CIPE delivery in each case. Cases of potential contamination will be reported, as the clinicians are instructed to report such cases to ERL.

### Data collection

Figure 2 presents the trials’ enrollment, intervention, and measurement schedule. Participants enrolled within 3 weeks after the incident are assessed with self-report measures at the time of enrollment (T0). All participants are subsequently assessed before randomization (T1), post-treatment (T2), and at 6-month (T3) and 12-month (T4) follow-ups. The main outcome will be measured at post-treatment (T2). Self-report data from participants are collected using an electronic survey solution offered by BASS at the Karolinska Institute, Stockholm. The same system is used to obtain written informed consent and to deliver CIPE. Links to questionnaires are sent to responders using SMS and email. Data from the therapists are collected using Nettskjema and Services of sensitive data (TSD) at the University of Oslo (see “data management and storing”). The research coordinator monitors the data collection process and sends reminders to reduce attrition rates.

### Assessments

#### Primary outcome measure

The PTSD Symptom Checklist (PCL-5) [31] is a 20-item questionnaire that measures DSM-5-specified symptoms of PTSD. The total score ranges from 0 to 80, with higher scores indicating more severe symptoms. Items are rated on a 0 (“not at all”) to 4 (“extremely”) Likert-type scale. The PCL-5 has satisfactory psychometric properties in various trauma populations [40–42]. This study administers a validated Norwegian version of the PCL-5 [43, 44]. As the index trauma is only a few days before T0 for most participants, the recall period is revised to “since the traumatic event” for this measurement. The recall period is “the last week” at T1, and “the last month” at T3 and T4. PCL-5 constitutes the main outcome of this study.

#### Secondary outcome measures

The Clinician-Administered PTSD Scale for DSM-5 (CAPS-5) [32] is a 30-item structured interview, developed to assess current and lifetime PTSD diagnosis, as well as past-week PTSD symptoms. The instrument measures the 20 DSM-5 PTSD symptoms, in addition to the onset and duration of symptoms, related subjective distress, and functional impairment (social, occupational), amongst other aspects of the disorder. Standardized questions and probes are provided. A Norwegian version of the CAPS-5 [45] is administered at T1 and T3–4. CAPS-5 has excellent psychometric properties [32, 46]. The recall period is 1 week at T1, and 1 month at T3 and T4.

The Mini-International Neuropsychiatric Interview (MINI) [33] version 6 is a brief, structured clinician-administered interview designed to assess 17 DSM/ICD diagnoses. Standardized questions and probes are provided. A Norwegian translation of the MINI [47] is administered at T1. The interview has good psychometric properties [33, 48, 49].

A Norwegian version [50] of the Stressful Life Events Screening Questionnaire (SLESQ) [51] is administered at T1 to measure self-reported lifetime exposure to traumatic events. The respondents are asked to report exposure to 15 categories of traumatic events (“yes” or “no”), age at the time of the incident, as well as frequency and duration of the events. Other aspects of the incidents are reported, as well. The Norwegian version of the SLESQ incorporates two extra items compared to the original 13-item version: “Have you ever been directly affected by a natural disaster?” and “Has anyone outside your family, such as fellow pupils or colleagues, repeatedly ridiculed you, put you down, ignored you, or told you were no good?”. The SLESQ has satisfactory validity and reliability [51, 52].

The Patient Health Questionnaire (PHQ-9) [53] is a 9-item self-report measure of depressive symptom severity. The recall period is 2 weeks. Response is given on a 4-point Likert-type scale (0: not at all, 1: several days, 2: more than half the days, and 3: nearly every day), resulting in a total score ranging from 0 to 27. Higher scores indicate higher symptom severity. The instrument is sensitive for both clinical and sub-clinical levels of depressive symptoms and has good psychometric properties [53, 54]. We administer a validated Norwegian version of the PHQ-9 [55].

The Insomnia Severity Index (ISI) [56] is a 7-item questionnaire that measures insomnia symptoms during the past 2 weeks. The instrument utilizes a 5-point Likert-type scale ranging from 0 to 4, yielding a total score of 0–28. Higher scores indicate more insomnia symptoms. The ISI has good psychometric properties [56–58]. A Norwegian version of the ISI is applied.

The Client Satisfaction Questionnaire (CSQ-8) [59] is an eight-item measure of participants’ service satisfaction. Response is given on a scale ranging from one to four, with a resulting total score ranging from 8 to 32. Higher scores suggest higher service satisfaction. A validated Norwegian version of the CSQ-8 is applied [60]. The CSQ-8 is adapted to the context of psychosocial crisis teams in the current trial (e.g., “treatment” adapted to “support”, “therapy” adapted to “support”).

The Traumatic Grief Inventory-Self Report Plus (TGI-SR+) [61] is a 22-item self-report questionnaire measuring symptoms of DSM-5 persistent complex bereavement disorder (PCBD) and ICD-11 Prolonged grief disorder (PGD) in participants who experienced traumatic bereavement. Response is given on a 5-point Likert-type scale ranging from 1 (“never”) to 5 (“always”). The total score ranges from 22 to 110, with higher scores indicating more severe symptoms. The instrument, including the Norwegian version applied here, has good psychometric properties [62, 63]. The instrument is administered at a 12-month follow-up and applies a recall period of the past month.

The EuroQol 5‑Dimension 5‑Level Questionnaire (EQ-5D-5L) [64] assesses self-reported health-related quality of life. It has five items: self-care, mobility, pain/discomfort, usual activities, and anxiety/depression, each measured on a 5-level severity scale (no, slight, moderate, severe, or unable/extreme problems). The instrument defines 3125 possible health states, valued by a representative sample of the general Norwegian population using the hybrid valuation method—composite time-trade-off and discrete choice experiment [65]. The utility scores are anchored on a − 0.453—1 scale, with 1 indicating “full-health,” 0 equivalent to “being dead,” and values below 0 are worse than being dead. The EQ-5D-5L data are used to generate quality-adjusted life year (QALY) used for cost-utility analysis (CUA). The instrument has excellent psychometric properties [66].

The recovering quality of life (ReQoL) is an 11-item outcome measure assessing psychopathology-specific quality of life in mental health contexts [67]. For each item, response is given on a 5-point scale (never to most of the time or always). The study also uses the ReQoL utility index (ReQoL-UI), which is a recovery-focused generic preference-based measure derived from ReQoL. ReQoL-UI constitutes six mental health items (activity; belonging; choice, control, and autonomy; hope; self-perception; and well-being) and a physical health item, each with five severity levels. The ReQoL-UI defines 78,125 different health states valued by a representative member of the UK public using a conventional time-trade-off method [68]. The ReQoL-UI is also used to generate QALYs for CUA in mental health interventions. The ReQoL-UI values range between − 0.195 (for the worst health state) and 1 (for the full-health state), with zero indicating a health state equivalent to being dead.

#### Other collected data

A structured adverse events (AE) questionnaire applied in the aforementioned RCT of CIPE [17] is utilized. The questionnaire was used in a previous trial with similar results to face-to-face interviews [69]. The instrument captures the frequency, duration, and nature of possible adverse events, and such events are further classified based on their perceived association with CIPE (related or unrelated). Both participants and clinicians are asked to report and rate participants’ short- and long-term discomfort of any AEs on a scale from 0 (“did not affect me at all”) to 3 (“affected me very negatively”).

In both TAU and CIPE, all time and resource use of therapists (i.e., treatment, travel, online tasks, appointments, preparation, and competence level of therapists) are registered. Registry data is also utilized for all participants, using the Norwegian Patient Register (NPR), Control and Payment of Health Reimbursement (KUHR), Municipal patient- and user-register (KPR), and FD-Trygd. However, in the absence of reliable registry data on the use of health care resources in the municipalities, this study applies survey data reported every second month by the crisis teams’ personnel, via a generic questionnaire. Consultation duration, type (e.g., CIPE, grief support, practical support), and mode (e.g., telephone, video consultation, home visit), as well as the professional background of the involved personnel, are reported from T1 to T4.

In the CIPE + TAU-arm, both clinicians and participants are assessed with a nine-item generic, unvalidated self-report measure of reasons for drop-out from CIPE, in cases where the participant did not finish CIPE. The questionnaire maps lack of motivation, disliking of e-therapy, lack of relevance, lack of reduction of PTSS, worsening of PTSS, remission, concurrent therapy elsewhere, and other (qualitative response category) as possible sources of drop-out. Response is given in one of two categories (0: no, 1: yes), except for the mentioned qualitative item.

Participants are also asked to self-report sociodemographic and background data: year of birth, gender, relationship and cohabitation status, country of birth (self and parents), educational and employment status, current use of psychotropic medication, current psychological treatment (outside of the trial), and ongoing threats or violence.

### Statistical analyses

H1–3 are tested with linear mixed effects models. The linear mixed effects model includes fixed effects for treatment group (intervention vs. control) and time (post-intervention, 6 and 12 months). In a hierarchical setup, a second step includes a treatment × time interaction. Random effects include random intercepts for participants to account for individual differences. The mixed effects models are applied using the R package nlme [70]. H4–6 are examined using independent t-tests. The quality-of-life change (change in QALY) of participants in CIPE vs. TAU (H6) is analyzed using the mixed effects model. Estimation is conducted using restricted maximum likelihood, with all available observations included, yielding unbiased estimates under the assumptions of missing at random or missing completely at random. For the t-tests, missing data are handled using multiple imputation.

Hypothesis 7 involves a comprehensive economic evaluation comparing the cost-effectiveness of CIPE relative to TAU in terms of both costs and consequences/effectiveness [71]. Costs are assessed using the ingredients approach, which involves three steps: first, identifying each resource required for the intervention; then, measuring these resources; and finally, valuing them. The effectiveness of the intervention is measured by QALY—a composite measure combining both quantity of life (mortality) and quality of life (morbidity) into a single metric [72]. For each arm, mean costs and mean QALYs are estimated across all participants to calculate the incremental cost (ΔC) and incremental effect (ΔQALY). The incremental cost-effectiveness ratio (ICER) or incremental cost per incremental QALY (ΔC/ΔQALY) is then calculated for decision-making. To accept the intervention, ICER should be less than the willingness-to-pay or cost-effectiveness threshold. Since there is no official threshold in Norway, we apply a threshold recommended by the Norwegian Directorate of Health (NOK 500 000 at 2005 prices), adjusted to current price levels [73].

This economic evaluation is conducted in two ways: trial- and model-based approaches. In the former, we compare trial-specific intervention costs and effects. Following recommendations by NICE [74], we perform a cost-utility analysis combining intervention-related and wider healthcare costs with changes in QALYs. In the latter, we develop a decision analytic model to simulate the long-term (lifetime) cost-effectiveness of CIPE. The model extrapolates beyond the trial period to estimate the potential lifetime costs and QALY outcomes under different assumptions. In both approaches, model parameter uncertainty is assessed using both probabilistic and deterministic sensitivity analyses.

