### Trial design

The EASE study is a hybrid Type 1 effectiveness and implementation trial [28] (for implementation, see section “implementation trial”). The first part of the study is a parallel two-armed multicenter randomized controlled add-on superiority trial, designed to randomize participants to either CIPE + TAU or TAU only (ratio 1:1). All participants will be offered ordinary crisis team services throughout the trial period. The CIPE group will be given CIPE as an add-on between T1 (4–7 weeks after trauma, dependent on the time of enrollment) and T2 (10–13 weeks after trauma, dependent on the time of T1 [i.e., T2 is always 6 weeks after T1]; see Fig. 1). For those included within 3 weeks from the incident, a screening assessment is performed at the time of recruitment (T0). Baseline assessment and evaluation of inclusion and exclusion criteria will be completed at T1. Outcome measures are gathered 6 weeks post randomization (T1), and follow-up measurements are accomplished at 6- and 12-month post PTE. This trial follows the SPIRIT guidelines and methodology [29] (see Additional file 1 for the SPIRIT checklist).

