### Inclusion and exclusion criteria

Inclusion criteria are (a) persons that receive support from a municipal crisis team, after (b) exposure to a traumatic event (as defined by criteria A of the PTSD diagnosis in the DSM-5) [30] within 4 to 7 weeks before T1, (c) a total score of 10 or above on the PTSD Symptom Checklist (PCL-5) [31] at T1 (4–7 weeks post trauma, dependent on the time of inclusion), (d) age 16 or above, (e) written informed consent, and (f) writes and speaks Norwegian and/or English.

Exclusion criteria are (a) severe psychopathology (e.g., psychotic symptoms, or high suicide risk) or substance dependence syndrome in need of specialized health care (harmful use is not an exclusion criteria, as long as participants commit to not being under the influence when completing the intervention), (b) known or evident severe cognitive impairment, (c) ongoing traumatization, violence, or threats, (d) unstable dose of psychotropic medication 2 weeks prior to T1, and (e) concurrent therapy elsewhere at the time of T1.

The therapists in the current trial are crisis team health care workers in the included sites (most commonly nurses and social workers). All therapists received training in study procedures. Those delivering CIPE were required to undergo training in CIPE (see the “Therapist training and fidelity” section).

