### Protocol violations and revisions

All included participants are included in the intent-to-treat analyses. Participants who do not complete CIPE within T2, or report adjustment of psychotropic medication or concurrent therapy elsewhere, as well as ongoing traumatization, violence, or threats after T1, and drop out of the trial, are not included in the completers’ analyses. Protocol revisions have been and will be updated in the clinical trial registry and communicated to REK for approval in accordance with the contract.

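### The primary mixed model lists no T1 PCL-5 term, which gives up precision and leaves the treatment contrast exposed if severity-related dropout differs by arm

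*Protocol article*

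**What the plan says.** The Statistical analyses section assigns H1–H3 to linear mixed effects models and names the terms: "The linear mixed effects model includes fixed effects for treatment group (intervention vs. control) and time (post-intervention, 6 and 12 months". A second step adds treatment × time. The only other component is a participant intercept: "Random effects include random intercepts for participants to account for individual differences". Estimation is by REML "with all available observations included, yielding unbiased estimates under the assumptions of missing at random or missing completely at random".

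On baseline data, the Inclusion and exclusion criteria section requires "a total score of 10 or above on the PTSD Symptom Checklist (PCL-5) [31] at T1", and the Data collection section says "All participants are subsequently assessed before randomization (T1), post-treatment (T2), and at 6-month (T3) and 12-month (T4) follow-ups". T1 PCL-5 is therefore known for every randomised participant. The Data collection section names T2 as the time of the main outcome.

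On the analysis set, the section on protocol violations and revisions says: "All included participants are included in the intent-to-treat analyses".

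**The concern.** The listed model starts at T2. The T1 value of the primary outcome, which should predict the T2 value, enters neither as an outcome row nor as a listed covariate. Three things follow.

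- **Precision.** The between-person variance that T1 could explain stays in the error of the treatment contrast.
- **Missing data.** For a participant with no T2, T3 or T4 score, the model can condition on nothing but arm. Dropout that depends on T1 is missing at random given T1, but this model does not use T1. If that dependence differs by arm, the groups still under observation are no longer comparable.
- **Who is analysed.** A participant with no follow-up score has no row in the model, so the intent-to-treat statement promises more than the model delivers.

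The primary comparison is at stake in both its precision and, under some dropout patterns, its centring.

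**Working it through.** **Inputs from the article** (Power and sample size calculations): d = 0.3, α = 0.05, 95% power, 150 participants (73 per group minimum), 183 after 20% attrition, recruitment target 360. Sidedness is not stated; two-sided is assumed. The T1–T2 correlation r is not given; 0.3 to 0.7 is assumed.

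**The plan's own figure.** For two means, n per arm = 2(1.960 + 1.645)²/0.3² = 289, not 73. So 150 does not follow from d = 0.3 in a plain two-group comparison. That is a separate issue; it matters here only because it sets the 45% starting point below.

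**Power with and without T1.** Adjusting for T1 multiplies the error variance by (1 − r²), so power ≈ Φ(d√(n/2)/√(1 − r²) − 1.96).

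- At 75 per arm, d√(n/2) = 0.3 × √37.5 = 1.837.
- At 144 per arm (360 less 20% = 288), it is 0.3 × √72 = 2.546.

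| r | 1 − r² | Power, 75 per arm | Power, 144 per arm | n per arm for 95% power |
|---|---|---|---|---|
| T1 not used | 1 | 45% | 72% | 289 |
| 0.3 | 0.91 | 49% | 76% | 263 |
| 0.5 | 0.75 | 56% | 84% | 217 |
| 0.7 | 0.51 | 73% | 95% | 148 |

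Leaving T1 out costs the equivalent of 1/(1 − r²) − 1 = 10%, 33% or 96% more participants.

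This is a single-time-point approximation. A simulation (500 replicates, 91 per arm, about 20% with no follow-up, compound-symmetric correlation treated as known) agrees. At r = 0.5 with random dropout, the standard deviation of the estimate was 0.163 without T1, 0.145 with T1 as a covariate, and 0.144 with T1 as an outcome with equal arm means.

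**Bias.** Take a true effect of zero, T1 as standard normal, one follow-up time, and logistic dropout on T1. Without T1 in the model, bias = r × (mean T1 of CIPE stayers − mean T1 of TAU stayers). The mean T1 of stayers is:

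- -0.191 at 30% dropout with log-odds 0.7 per SD;
- -0.130 at 20% with 0.7;
- -0.069 at 20% with 0.35;
- 0 if dropout is random.

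At r = 0.6:

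| CIPE dropout | TAU dropout | Bias (SD) |
|---|---|---|
| 20%, log-odds 0.7 | 20%, log-odds 0.7 | 0 |
| 30%, log-odds 0.7 | 20%, log-odds 0.7 | -0.037 |
| 20%, log-odds 0.7 | 20%, log-odds 0.35 | -0.037 |
| 20%, log-odds 0.7 | 20%, random | -0.078 |
| 30%, log-odds 0.7 | 20%, random | -0.115 |

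A simulation of the last row gave -0.118, and a value within 0.005 of zero once T1 was in the model. Negative values favour CIPE. The dropout rates by arm and the log-odds are assumptions; the article gives 20% attrition, not split by arm.

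**Participants without a row.** 0.20 × 183 = 36.6, so at most about 37. At the recruitment target, 0.20 × 360 = 72. Both are upper bounds, because someone who misses T2 may return at T3 or T4.

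**The case against.** The strongest reply is that this is a condensed article. It says the model includes certain effects, not that it includes only those, and covariates are often left to an analysis plan. This stands in part. The named time levels settle that T1 is not an outcome row; that T1 is not a covariate is inferred from a list that omits it. But the list is explicit enough that an analyst following it would leave T1 out. Nor does it help to read T1 as an unnamed reference level: the first step, without an interaction, would then average the treatment effect over a pre-randomisation visit.

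A reader might go further and infer that the model contradicts the intent-to-treat statement and that the missing-at-random claim fails. The documents do not support this.

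- The claim is conditional: "yielding unbiased estimates under the assumptions of missing at random or missing completely at random". If dropout depends on T1 equally in both arms, at the same rate, the treatment contrast is not biased. The claim is too broad, not false in every case.
- A likelihood analysis of all available outcomes is a common way to implement intent-to-treat, and the article sets it against a completers' analysis. The number with no follow-up at all is not given.
- Nothing in the article shows that severity drives loss of data. The listed reasons for leaving CIPE are varied and include remission, and leaving CIPE is not the same as missing questionnaires.

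It is also fair that the 45% figure owes much to the sample-size calculation. At 144 per arm the gain is smaller in absolute terms, except at high correlations.

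**Conclusion.** The point holds as a weakness in the primary analysis that should be corrected. The listed terms omit the T1 value of the primary outcome, which every randomised participant has. The precision loss follows for any non-zero T1–T2 correlation; its size, 4 to 28 percentage points of power at 75 per arm and 4 to 23 at 144 per arm, rests on the assumed range of 0.3 to 0.7.

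The bias is conditional. It is zero when dropout is equally frequent and equally related to T1 in both arms, and about -0.12 SD (40% of d = 0.3) in the most unfavourable scenario tried, at r = 0.6. Including T1 removes it.

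The intent-to-treat wording is looser than the model, by at most about 37 of 183 participants. That is a mismatch to tidy, not proof that the analysis breaks intent-to-treat. Baseline adjustment does not rescue the stated sample size either: 95% power with 75 per arm would need 1.837/√(1 − r²) = 3.605, or r of about 0.86.

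**What to change.** State how T1 PCL-5 enters the primary model, by one of two routes.

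1. **T1 as covariate.** Add T1 PCL-5 and T1 × time as fixed effects. This recovers the precision and removes the bias described above. It does not bring back participants with no follow-up score, so the intent-to-treat sentence would need rewording to say who contributes.
2. **T1 as outcome.** Add T1 to the outcome vector with the arm means constrained equal at T1. This does the same and keeps every randomised participant. A random intercept alone would force equal variances and correlations across T1–T4. That is doubtful when T1 is cut off below 10 and its recall period differs from T3 and T4, so specify a less restrictive covariance structure.

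The second route fits the intent-to-treat statement better; precision is nearly the same. Apply the same approach to PHQ-9 and ISI where a T1 value is collected (the schedule figure is not shown).

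The cost is a short amendment, plus the covariance choice under the second route. No new PCL-5 data are needed. The Trial status section puts the end of recruitment at September 2026, the Blinding section says the statistician is blinded, and the article describes a revision route through the registry and the ethics committee. Make the change before unblinding.

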## Method

### Research context

Twenty-one municipal crisis teams from the central-eastern parts of Norway participate in the study. The crisis teams are chosen to deliver the intervention due to their aforementioned role in the Norwegian health care system and the well-organized psychosocial services already offered by these teams. Participation requests were directed to municipal crisis teams by the Regional Resource Center for Violence, Traumatic Stress, and Suicide Prevention (RVTS East) to ensure variation in municipal population size, and municipalities from both rural and urban areas. A list of study sites is available in the trial registration (ClinicalTrials.gov identifier: NCT06592677).

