### Randomization

Eligible participants are randomized 1:1 in random block sizes of 4, 6, or 8 to either CIPE + TAU or TAU only, using the Sealed Envelope software [36] at T1. To mitigate the risk of contamination across treatment conditions, participants from the same household are cluster-randomized. The randomization is stratified on the level of municipal crisis teams to ensure an even distribution of cases in each treatment condition across municipalities. An independent, blinded senior researcher is responsible for all randomization procedures. The allocation is revealed to the study coordinator only after the T1 assessment and decision of inclusion are completed.

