#### TAU

Participants in the TAU condition receive standard psychosocial support that is routinely provided by the crisis teams. This could include a varying number of consultations (typically 1–4) consisting of psychoeducation and normalization of symptoms of acute stress, activation of the victim’s social network, practical support, and/or grief support [20]. Although common practice is to follow the guidelines from the Norwegian Directorate of Health [20], there is considerable heterogeneity in what constitutes TAU within and between different crisis teams. This applies both to the content and frequency of support. There are no available detailed descriptions (scientific, official statistics, or other available information) of what TAU constitutes within or across services. Thus, consultation frequency, duration, type, and mode are assessed (see the “Other collected data” section).

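### Randomisation is stratified by 21 crisis teams, but no stated analysis includes crisis team; taken alone this costs a little precision in the between-arm comparison, without bias

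*Protocol article*

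**What the plan says.** All references are to the protocol article.

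- **Research context:** "Twenty-one municipal crisis teams from the central-eastern parts of Norway participate in the study".
- **Randomization:** "The randomization is stratified on the level of municipal crisis teams to ensure an even distribution of cases in each treatment condition across municipalities". Allocation is by permuted blocks: "Eligible participants are randomized 1:1 in random block sizes of 4, 6, or 8". In addition, "participants from the same household are cluster-randomized".
- **TAU:** the article reports that "there is considerable heterogeneity in what constitutes TAU within and between different crisis teams", in both content and frequency of support.
- **Statistical analyses:** for H1–3, "The linear mixed effects model includes fixed effects for treatment group (intervention vs. control) and time (post-intervention, 6 and 12 months"), with treatment by time added in a second step. "Random effects include random intercepts for participants to account for individual differences". H4–6 use independent t-tests, apart from the quality-of-life part of H6, which uses the mixed model.

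Crisis team is not named as a fixed effect, random effect or covariate in any analysis. Household is not named either.

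**The concern.** Stratifying by team balances the arms within each team, so differences between teams largely drop out of the true sampling variance of the treatment contrast. A model without team does not know this. It counts between-team variance as ordinary between-participant variance (in the mixed model, within the participant intercept) and reports the larger, unstratified standard error. The precision that stratification was meant to buy is then partly lost.

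The article gives some reason to expect a team effect. Usual care differs between teams, both arms receive it, and most therapists deliver both conditions. A team effect would therefore be shared across arms, which is the kind of variance that stratification removes.

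The T2 primary comparison is affected. The listed time points are post-intervention, 6 and 12 months, so the T2 difference is a comparison between participants. At stake are the width of its confidence interval and some power. The estimate itself is not biased.

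**Working it through.** **Inputs from the documents.** 21 teams; 1:1 allocation in blocks of 4, 6 or 8; d = 0.3; 73 per group minimum; recruitment target 360, or 180 per arm. **Assumed:** the between-team ICC of the outcome, shown from 0.01 to 0.10. The documents give no value.

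**The plan's own figure.** The article states no standard error or ICC to reproduce. Its sample size (150, 73 per group, 95% power at d = 0.3) can be matched by a within–between interaction test with f = 0.15, two measurements and correlation 0.5. That test needs N = 148 and has power 0.950 at N = 146; 146/0.80 = 182.5, matching the 183. The article does not state these inputs. A plain two-group comparison at 95% power would need 289 per arm, which is why the power figures below start near 44% at 73 per arm.

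**Step 1: standard error, large-sample (outcome SD = 1).** A model without team reports SE = sqrt(2/n). Under stratified allocation the true SE is sqrt((2/n)(1−ICC)). The overstatement is 1/sqrt(1−ICC), and the actual size of the 5% test is 2[1−Φ(1.96/sqrt(1−ICC))].

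| Team ICC | SE overstated by | Actual type I error |
|---|---|---|
| 0.01 | 0.5% | 4.9% |
| 0.02 | 1.0% | 4.8% |
| 0.05 | 2.6% | 4.4% |
| 0.10 | 5.4% | 3.9% |

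For the treatment effect averaged over T2–T4, with an assumed within-person correlation of 0.5, the participant mean has variance 2/3. ICC is then replaced by ICC/(2/3), and the overstatement is 0.8%, 1.5%, 4.0% and 8.5%. In a treatment-by-time contrast a constant team effect cancels, so nothing is lost there.

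**Step 2: power for a simple T2 comparison at d = 0.3.** Without team: Φ((0.3 − 1.96·SE_reported)/SE_true). With team: Φ(0.3/SE_true − 1.96).

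- 73 per arm, SE_reported = sqrt(2/73) = 0.1655. ICC 0.05: SE_true 0.1613, power 44.0% → 46.0%. ICC 0.10: SE_true 0.1570, power 43.8% → 48.0%.
- 180 per arm, SE_reported = sqrt(2/180) = 0.1054. ICC 0.05: SE_true 0.1027, power 81.8% → 83.1%. ICC 0.10: SE_true 0.1000, power 82.5% → 85.1%.

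At ICC 0.01–0.02 the gain is under one point at either size.

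**Step 3: simulation.** 21 unequal teams, blocks of 4/6/8, 2,500 runs per scenario, Monte Carlo error of each SE ratio about 1.4%. At N = 360 and ICC 0.10, reported SE over true SE was 1.06 and type I error 3.9% without team; with team fixed effects they were 1.01 and 4.8%. At N = 146 and ICC 0.10, the figures without team were 1.02 and 4.2%, weaker than the closed form. A smaller run (500 trials per cell, N = 146, random team intercept) gave power 45.0% → 47.6% at ICC 0.05 and 43.0% → 45.8% at ICC 0.10.

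**Step 4: households.** If a share s of participants come in same-arm pairs and household adds a variance share ρ, the true variance factor is about 1 − ICC + sρ. With s = 0.40 and ICC = 0.05, ρ = 0.125 gives 1 − 0.05 + 0.05 = 1.00, an exact offset. Simulated at N = 146 with s = 0.40: team 0.05 and household 0.2 gave an SE ratio of 0.99 and type I error 5.6%; team 0.02 and household 0.3 gave 0.94 and 6.6%. All household values are assumed.

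**The case against.** **The full analysis plan may settle this.** Stratification covariates are often fixed there, and the article's wording (the model includes these terms) need not be exhaustive. That is fair, and it is one reason to keep the grade low. However, the section goes into detail: fixed effects, random effects, the two-step build, the R package, REML and missing-data handling. Followed as written, it leaves out the factor used to randomise.

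**The size is assumed.** This stands. The TAU section describes varied support, not PCL-5 scores that differ by team, and at ICC 0.01–0.02 the effect is negligible.

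**The teams are not necessarily tiny.** 146/21 ≈ 7 and 183/21 ≈ 9 per team, but at the recruitment target 360/21 ≈ 17, where the power gain is only 1.3–2.6 points.

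**A stronger reading.** A reader might infer that the trial's reported standard error will be too large and its primary test will run below 5%. The documents do not support that as a net result. Same-household participants share an arm, no household term is listed, and this pushes the standard error the other way. As Step 4 shows, it can cancel or outweigh the team effect. Nor do the documents support a claim of bias.

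**Conclusion.** The point holds in limited form. The stratification factor is missing from every stated analysis, and from that source alone the standard error of the between-arm contrast is overstated by roughly 0.5% to 5.4% for team ICCs of 0.01 to 0.10. The cost at d = 0.3 is about 2–4 power points at 73 per arm and 1.3–2.6 at 180 per arm for ICC 0.05–0.10. At 73 per arm the simulated gain was 2.6–2.8 points, so the upper figure is optimistic.

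This rests on an assumed ICC, a simple T2 comparison and a continuous outcome; the variance formula does not carry over directly to the binary outcomes. It says nothing about the net standard error, whose direction depends on household clustering that the documents do not quantify. It is a minor improvement, not a threat to validity.

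**What to change.** In Statistical analyses:

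- **Continuous outcomes in the mixed models (H1, H3, the quality-of-life part of H6):** add a random intercept for crisis team, with household nested within team and participant within household. nlme fits nested effects of this kind. Household belongs in the same change, since adding team alone would leave the opposing error in place.
- **Continuous outcomes now given t-tests (H4, H5):** replace the t-test with a regression or mixed model that includes team. H5 uses only bereaved participants, so numbers per team will be small.
- **Binary outcomes (H2 PTSD status, H6 referral):** use a corresponding generalised model with team. A linear nlme intercept does not serve here.

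A random team effect is preferable to 20 fixed effects when strata are small. At N = 146 and ICC 0.02, team fixed effects gave a slightly larger true SE than no team term (0.166 against 0.162). The smaller simulation found no cost from a random team intercept when the team ICC is zero; the full three-level nesting was not simulated.

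The cost is a few lines of wording, with no new data or participants. Recruitment is ongoing, so the terms can be fixed before any analysis.
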